### Outcome measures

2.5.

#### Primary outcome measures

2.5.1.

##### Y-balance test (YBT)

2.5.1.1.

The first primary outcome measure is the stability and balance of lower limbs evaluated by the Y-Balance Test (YBT). Y-Balance Test is a clinical instrument base on star excursion balance test (SEBT) which is commonly used for assesses dynamic stability and neuromuscular control of the lower extremity, and studies have proofed its reliability (30). The YBT will be assessed before and after Tuina treatment.

Before the YBT, participants will be instructed to learn the correct stretch technique and allowed four practice trials in each direction, with three consecutive test trials in each direction during testing. The order of the directions is random. Composite scores and two-sided differences will be calculated at the end of the test. The calculation formula is shown below. If the composite score is less than 95%, it indicates poor joint stability, and there may be a high risk of injury to the support leg, a lower score indicates a higher risk of injury. If bilateral difference is greater than 5%, it suggests a large difference in strength or balance between the left and right support legs, a higher difference indicates a higher risk. Studies have shown that patients with an anterior right/left reach distance difference greater than 4 cm would be 2.5 times more likely to sustain a lower extremity injury (31).$$\mathrm{Composite}\;\mathrm{score}=\frac{a+b+c}{L\times 3}\times 100\text{\%}$$$$\mathrm{Two}\text{-}\mathrm{sided}\;\mathrm{differences}=\frac{\left(a1+b1+c1)-(a2+b2+c2\right)}{(a1+b1+c1+a2+b2+c2)/2}\times 100\text{\%}$$Notes: *a*1, *b*1, *c*1, *a*2, *b*2 and *c*2 represent the farthest distance of the left/right foot extended in the three directions respectively. *L* represents the length of the leg.

##### Cumberland ankle instability tool (CAIT)

2.5.1.2.

The second primary outcome measure is self-assessment of ankle instability evaluated by Cumberland Ankle Instability Tool (CAIT). CAIT is an easy and understandable valid tool for the assessment of chronic ankle instability (32), and it can differentiate the stable and unstable ankle (33). Participants will rate their left and right ankles separately. Each question is assigned a different score based on the number of options. The maximum unilateral ankle score is 30. Participants with a unilateral ankle score equal or less than 27 are considered unstable on that side of the ankle and the range above it are considered stable (33).

#### Secondary outcome measures

2.5.2.

##### Ankle function

2.5.2.1.

Ankle function will be assessed by Foot and Ankle Ability Measure (FAAM). The FAAM is also a patient-completed rating scale consisting of a daily activities subscale (21 rated items) and a physical activity subscale (7 rated items) with response options on a 5-point Likert scale (4 to 0, respectively), which has been demonstrated reliable, to evaluate postural control and muscle strength in patients with CAI (34).

##### Ankle range of motion

2.5.2.2.

Ankle range of motion (ROM) will be assessed by limb goniometer. Ankle plantar flexion/dorsiflexion, varus and valgus range of motion will be measured, the method of measurement is shown below, and the angle of activity will be measured and recorded by the researcher.
(1)Ankle dorsiflexion range of motion: participants will move their weight forward, squat on one leg, land on their heels, and flex their knees to the maximum. The angle between the lower leg and the ground will be measured when the ankle is dorsiflexed to the maximum range of motion.(2)Ankle plantarflexion range of motion: participants will move their weight back, squat on one leg, land on the balls of their feet, and extend their knees to the maximum extent. The angle between the lower leg and the ground will be measured when the ankle is plantarflexed to the maximum range of motion.(3)Range of motion of ankle inversion and eversion: participants will move their weight to the left and right sides, squat on one leg, land on the balls of their feet, and maximize inversion and eversion their ankle. The angle between the lower leg and the ground will be measured when the ankle inversion and eversion to the maximum range of motion.

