### Randomization, allocation, and blinding

2.7.

We will use Statistical Package for the Social Sciences (SPSS) Ver.25.0 (IBM Inc, New York, USA) and manual assistance to complete randomization, the method is shown below.

Before the study, a randomization specialist, who will not join other part of this trial, will be set up, and the specialist will use SPSS Ver.25.0 to generate a set of random numbers according to the numbers 1–72. After that, the numbers will be sorted according to the order of random number from small to large, 72 numbers will be randomly divided into the intervention group and the control group, and the numbers and corresponding groups will be sent to the researchers. When the appropriate participants are recruited, the researchers will enter the form and number it according to the order of enrollment, and determined the group of the current case according to the grouping generated by the randomization specialist. The lists of the two groups are sorted into tables and sent to the doctor, who are informed of the treatment plan for each group in advance, in order to reduce unnecessary communication between researchers and randomization specialist in the grouping process, and avoid the influence of researchers' subjective will on the grouping as much as possible. The participants and the doctor will not be blinded because of specialization of Tuina. However, the data analysis and efficacy assessment will be performed by the research assistant, who will not join other part of this trial, and blinded in order to decrease analysis bias.

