### Data collection and management

2.8.

We will collect the baseline data before the study. The primary and secondary outcomes will be assessed at baseline and 4 weeks (at the end of the intervention). The researcher will collect the data in the case report form (CRF) after obtaining signed consent from the participants. To protect the privacy of the participants, we will use codes and initials instead of their personal information. After data uploading and confirming, only statistician can access to the data.

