## Discussion

3.

Holism is one of the characteristics of traditional Chinese medicine, during the process of diagnosing disease and treatment, how to apply the holistic concept and syndrome differentiation is one of the most important problems in clinical treatment. In the treatment of CAI, Tuina therapy is one of the common and effective treatment methods, and it can also combine the treatment of hip-knee-ankle in a good way, so we have designed a clinical trial for the application of Tuina in the treatment of chronic ankle instability. The aim of this study is to investigate the effects of Tuina based on the concept of hip-knee-ankle conjugation in patients with chronic ankle instability. The stability and balance of lower limbs will be assessed by Y-Balance Test and CAIT scores. The ankle function will be assessed by FAAM scores and ankle range of motion test. The study will attempt to explore the effect of hip-knee-ankle treatment on chronic ankle instability and provide evidence of the effects of Tuina in patients with CAI.

Decreased balance and impaired precise joint movement control are the main consequences of CAI, and recurrent ankle sprain is one of the important causes of this disease. These symptoms ultimately degrade the quality of life and athletic ability of patients with CAI. Although there are previous studies on hip-knee-ankle conjugate theory, they are most applied in the treatment of knee osteoarthritis. This study focus on the effect of hip-knee-ankle conjugate theory on the treatment of CAI, in order to explore how to improve the stability and balance of lower limbs and ankle function by using manipulation and improve the quality of life and motor ability of the patients with CAI.

Although the aim of this trial is to explore the effect of Tuina on ankle injuries and address the limitations of previous studies, this study also has its own limitations. First, because it is impossible to blind the doctor and participants, it is difficult to design a double-blinded RCT. To minimize the risk of detection bias, we have a randomization specialist, he will divide the participants into two groups randomly prior to the study, the assessors and analyst will be blinded to the group assignment in this study. Second, due to lack of precision instruments, lower limb stability, balance ability and ankle range of motion can only be assessed manually, which inevitably leads to certain errors.

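### Ankle ROM is assigned to the researcher in one section and to a blinded research assistant in another, and the assessor-blinding claim cannot cover the self-rated CAIT and FAAM

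*Protocol article*

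**What the plan says.** Four statements in the protocol article bear on who assesses outcomes.

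- **Section 2.7 (Randomization, allocation, and blinding)** separates four roles: a randomization specialist, the researchers, the treating doctor and a research assistant. On assessment it says that "the data analysis and efficacy assessment will be performed by the research assistant, who will not join other part of this trial, and blinded". On allocation it says that "the numbers and corresponding groups will be sent to the researchers", and that the researchers then "determined the group of the current case according to the grouping generated by the randomization specialist". On the remaining parties: "The participants and the doctor will not be blinded because of specialization of Tuina".
- **Section 2.5.2.2 (Ankle range of motion)** says that "the angle of activity will be measured and recorded by the researcher".
- **Section 2.8 (Data collection and management)** uses the same role name for the data: "The researcher will collect the data in the case report form (CRF").
- **Section 3 (Discussion)** acknowledges that doctor and participants cannot be blinded and, as its answer to detection bias, states that "the assessors and analyst will be blinded to the group assignment in this study".

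On the instruments, Section 2.5.1.2 describes CAIT as a self-assessment in which participants score each ankle, and Section 2.5.2.1 describes FAAM as completed by the patient. CAIT is the second primary outcome. FAAM and ROM are secondary. The YBT section (2.5.1.1) names no assessor, so only the general statement in 2.7 covers it.

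**The concern.** In an open-label trial of a manual therapy, blinded outcome assessment is the main protection against detection bias, and the article relies on it explicitly. Two things weaken that reliance as the text stands.

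First, the same task is given to two different roles. Staff who follow 2.5.2.2 and 2.8 as written would have ROM read and recorded by the role that receives the group list and assigns cases. The Discussion concedes that ROM can only be measured manually and with some error. A manual reading leaves room for an observer's expectation to act.

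Second, for CAIT and FAAM the person giving the score is the participant, who knows the arm. An assistant who hands out or scores the form cannot blind that rating. An unqualified claim of blinded efficacy assessment therefore promises more than the design can deliver for one primary and one secondary outcome.

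**Working it through.** This is a check of roles against outcomes. The article has no figure of its own to reproduce on this point.

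**Step 1: who holds the allocation.** Under Section 2.7 the researchers receive the numbers with their groups and determine each case's group at enrolment. The doctor and the participants are unblinded. The research assistant is said to be blinded and to take no other part.

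**Step 2: who produces each outcome value.**

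| Outcome | Rank | Who rates or measures it, by its own section | Does the 2.7 assessor blinding reach it? |
|---|---|---|---|
| YBT | primary | no one named (2.5.1.1) | yes, through the general statement |
| CAIT | primary | participant (2.5.1.2) | no, the rater is unblinded |
| FAAM | secondary | participant (2.5.2.1) | no, the rater is unblinded |
| ROM | secondary | the researcher (2.5.2.2) | contradictory: 2.7 says the research assistant |

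**Step 3: can the two ROM statements both hold?** They can only if the researcher in 2.5.2.2 is the research assistant of 2.7. But 2.7 uses the two terms for different people, and one of them receives the list. An assistant with no other part in the trial cannot also be the person who enrols and assigns. Section 2.8 does not settle it. Collecting data in the CRF could be plain data handling, but it uses the same role name and so leans towards the literal reading of 2.5.2.2.

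**Step 4: count.** One outcome of four (ROM) has a contradictory assessor. Two of four (CAIT and FAAM), including one of the two primaries, fall outside assessor blinding by their nature. Blinded data analysis, also stated in 2.7, applies to all four.

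**Step 5: what a bias would do, on an assumption.** The article gives no size for a rating bias, so the range here is assumed. Take one continuous outcome, 36 per group (Section 2.6), no true effect, and a differential bias of b standard deviations. The shift in the test statistic is b / √(2/36), and the two-sided 5% false-positive rate is 1 − Φ(1.96 − shift) + Φ(−1.96 − shift).

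| Assumed b (SD) | Shift | False-positive rate |
|---|---|---|
| 0 | 0 | 5% |
| 0.1 | 0.42 | about 7% |
| 0.2 | 0.85 | about 14% |
| 0.3 | 1.27 | about 25% |
| 0.5 | 2.12 | about 56% |

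This shows only that a modest bias would matter at this sample size. It is not an estimate of bias in this trial. The sample size calculation is unaffected.

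**The case against.** The strongest reply is that Section 2.7 governs blinding, ROM is an efficacy outcome, and so the blinded assistant already covers it. On that view the wording in 2.5.2.2 sits in a description of measurement technique and may simply mean whoever holds the goniometer. This stands to the extent that the text is a contradiction and not proof of an unblinded ROM assessor. It does not remove the need to reconcile the sections, because staff cannot tell which one to follow.

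The second reply is that unblinded self-report is unavoidable here and is disclosed: 2.7 says participants are not blinded, the Discussion lists this as a limitation, and both scales are described as self-completed. That also stands. What remains is narrower. The Discussion offers blinded assessors as the remedy without saying that two outcomes lie beyond its reach.

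Several stronger readings are tempting, and the article does not support them:

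- **Three of the four outcomes are unblinded as planned.** For ROM this treats an ambiguous role name as fact.
- **The safeguard protects only YBT.** Blinded analysis covers every outcome.
- **The extra hands-on time in the Tuina arm is part of this problem.** It follows from an openly stated add-on design and concerns performance effects, not who assesses outcomes.
- **The conclusion should rest on YBT alone.** That would re-rank two stated primaries, a debatable trade-off that this point does not require. The Discussion's remark on manual error also names stability and balance, so YBT depends just as much on the assessor being blinded.

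**Conclusion.** The point holds in two limited parts. Sections 2.5.2.2 and 2.8 conflict with Section 2.7 over who measures and records ROM, and the literal reading of 2.5.2.2 would defeat the blinding that 2.7 and the Discussion claim for that outcome. In addition, the unqualified assessor-blinding statements cannot be true of CAIT and FAAM, one of which is primary.

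The first part assumes that the article's role names are used consistently. If the researcher was meant to be the blinded assistant, only the wording is wrong. The second part needs no assumption beyond what the article says about the scales and about participants. The documents do not allow the size of any bias to be stated. The trial can run as designed, but the text should be corrected before outcomes are assessed and reported.

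**What to change.** 1. In Sections 2.5.2.2, 2.7 and 2.8, state that the blinded research assistant, with no access to the allocation list, measures and records YBT and ROM at baseline and at week 4, and that the researcher who holds the list takes no outcome measurement.
2. In Section 2.7 and the Discussion, limit the assessor-blinding claim to YBT and ROM. State that CAIT and FAAM are self-reports by unblinded participants, and that the data analysis is blinded for all outcomes.

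The cost is a few sentences and, at most, one task moved between staff already named. No change to visits or sample size is needed. The downside is a more modest claim for CAIT and FAAM.

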**Methods:**

We have designed a randomized controlled trial. A total of 72 participants with CAI will be randomly divided into functional training groups and hip-knee-ankle Tuina combined with functional training group in a 1:1 ratio. Participants in control group will receive 8 sessions of functional training (30 min per session, twice a week for 4 weeks). Participants in intervention group will receive 8 sessions of Tuina combined with functional training (twice a week for 4 weeks). The primary outcomes include the Y-Balance Test (YBT) and Cumberland Ankle Instability Tool (CAIT). The Secondary outcomes include the Foot and Ankle Ability Measure (FAAM) and ankle range of motion (ROM). The outcome assessments will be conducted before the first intervention and after the last intervention.

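### Plantarflexion is read from the lower leg to the ground while the participant stands on the ball of the foot, so on the natural heel-raised reading the recorded angle does not measure plantarflexion

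*Protocol article*

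**What the plan says.** Ankle range of motion is part of the stated objective (Background; 2.1 Objectives) and one of the two secondary outcomes (Abstract, Methods; 2.5.2). Section 2.5.2.2 names the instrument, "Ankle range of motion (ROM) will be assessed by limb goniometer", and then sets a posture and an angle for each movement:

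- **Dorsiflexion:** weight forward on one leg; participants "land on their heels, and flex their knees to the maximum". The angle is lower leg to ground.
- **Plantarflexion:** weight backward; participants "squat on one leg, land on the balls of their feet, and extend their knees to the maximum extent". The rule for the angle is: "The angle between the lower leg and the ground will be measured when the ankle is plantarflexed to the maximum range of motion".
- **Inversion and eversion:** weight to either side on one leg; participants "land on the balls of their feet, and maximize inversion and eversion their ankle". The rule for the angle is: "The angle between the lower leg and the ground will be measured when the ankle inversion and eversion to the maximum range of motion".

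The ground is the reference line in all three. The foot is never named as a reference segment. No neutral-position reading or correction for the inclination of the foot is described, and no other section of the article gives a different method.

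**The concern.** Ankle motion is the movement of the lower leg relative to the foot. The ground can stand in for the foot only while the foot lies level on it in the plane being measured. The dorsiflexion test meets that condition because the heel is down. The plantarflexion test, read naturally, does not: on the ball of the foot the heel is up and the foot is inclined, yet the reading is still taken to the ground.

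At stake is one component of a secondary outcome, and to a lesser degree a second. A real difference between groups in plantarflexion could go unseen. A change in how participants hold the lower leg between baseline and week 4 could be reported as a change in range of motion. This is a fault in the definition of the measurement and not a detail left to a fuller protocol, because the article states both the posture and the angle.

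**Working it through.** The plan gives no figure that depends on this point, so there is none to reproduce. The check is plane geometry. Postures and recorded angles come from section 2.5.2.2; all tilt and pitch values are illustrative assumptions, since the article gives none.

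**Plantarflexion (side view).** Let t be the forward tilt of the lower leg from vertical (negative if it leans backward) and h the pitch of the foot above the ground from heel lift.

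- Recorded angle = 90 − t
- Plantarflexion (neutral = 0) = h − t

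The recorded angle does not contain h.

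| t | h | Recorded angle | Plantarflexion |
|---|---|---|---|
| 0 | 20 | 90 | 20 |
| 0 | 50 | 90 | 50 |
| 10 | 20 | 80 | 10 |
| 10 | 50 | 80 | 40 |
| −10 | 20 | 100 | 30 |
| −10 | 50 | 100 | 60 |

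In each pair the reading is the same and plantarflexion differs by 50 − 20 = 30 degrees. The result needs equal lower-leg tilt within the pair, not a vertical lower leg.

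The error also runs the other way. With t = 0 and h = 20, plantarflexion is 20 − 0 = 20 and the reading is 90. With t = 10 and h = 30, plantarflexion is 30 − 10 = 20 and the reading is 80. The reading moves by 10 degrees with no change at the ankle.

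**Dorsiflexion, heel down (h = 0).** The ankle angle depends on t alone, so 90 − t fixes it. The ground reference works here.

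**Inversion and eversion (front view).** What matters is side-to-side roll of the sole, not heel lift. Let s be the sideways tilt of the lower leg and r the roll of the sole.

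- Recorded angle = 90 − s
- Motion relative to the foot = s + r

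At s = 10 the reading is 80. The motion is 10, 20 or 30 degrees for r = 0, 10 or 20. With r = 0 the reading captures all of the motion; otherwise it captures part of it. The article neither requires nor rules out r = 0.

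**The case against.** The strongest reply is that the text never says the heel is raised. The plantarflexion instruction starts with a backward weight shift, mirroring the forward shift for dorsiflexion, so the pair could mean leaning forward and then backward over a planted foot. With the sole down (h = 0), plantarflexion is −t and the recorded angle is 90 − t, so the method would work. The English is loose throughout, and part of the problem may be wording. This earns a stated assumption, but it does not remove the point: the instruction places the participant on the ball of the foot, in contrast to the heel contact given for dorsiflexion, and nothing elsewhere restores a flat foot.

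A reader might infer that the reading would sit at about 90 degrees whatever the ankle does. The documents do not support that. It assumes a vertical lower leg, which the backward weight shift does not guarantee.

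A reader might also infer that three of the four directions are invalid. That does not hold either. For inversion and eversion, standing on the ball of the foot pitches the foot front to back, whereas the relevant movement is side-to-side roll, and the reading can carry some or all of it.

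The request to squat and extend the knee fully in the same manoeuvre is an ambiguity of wording, since full extension may mean as far as that position allows. It adds little. The Discussion concedes some error from manual assessment, but that concerns precision and does not cure a wrong reference line. Measuring both groups alike does not recover motion that is not recorded.

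**Conclusion.** The point holds for plantarflexion. On the heel-raised reading, the recorded angle reflects lower-leg tilt and omits foot pitch, so it does not measure plantarflexion. The 30-degree example shows what the definition can miss; it is not an estimate of the error in this trial, because actual tilts and pitches are unknown. For inversion and eversion the measure is imperfectly isolated and needs clarification, but it is not shown to be invalid.

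The conclusion rests on one assumption about posture, that standing on the ball of the foot means the heel is off the ground. If the sponsor intended a flat foot, the method may be sound and the wording is what needs correcting.

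The reach is limited. Heel-down dorsiflexion, the other secondary outcome (FAAM) and the two primary outcomes are unaffected. So is the sample size, which section 2.6 bases on the Y-Balance Test. The change should be made, but it does not threaten the main comparison.

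**What to change.** In section 2.5.2.2 and the case report form:

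1. Keep the lower-leg-to-ground angle for heel-down dorsiflexion.
2. For plantarflexion, record the angle between lower leg and foot with the same goniometer, in one fixed and described position.
3. For inversion and eversion, either use the same leg-to-foot reference or require the sole to stay flat side to side while the ground angle is read.

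The cost is revised wording, an updated case report form and brief retraining of the assessors. Instrument and visits stay the same. The downside is that values already taken under the current definition cannot be pooled with new ones and must be analysed separately. Change from baseline needs the same definition at both visits, so the switch is cleanest for participants not yet measured at baseline.
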